**Fig. 2 Fig2:**
[figure not shown]
The overview of intervention targets, sessions in perioperative stage and rehabilitation stage, and adopted VR techniques

Based on Unity software (version 2018.3.11fl), we developed a self-led VR-CBT app that included comprehensive components of CBT in collaboration with School of Computer Science and Engineering, Sun Yat-sen University. The desktop VR application, classified as non-immersive in comparison to VR solutions using a head-mounted display, was adopted in this study. The avatars and structures constructing the virtual environment were built using Blender 2.83. The app has been registered in Copyright Protection Centre of China (Certificate No.11288804), and has been licensed by the Ministry of Industry and Information Technology of China (No. ICP 2022124889). The first phase of this app development involved an extensive, iterative process with numerous rounds of user testing. The app is designed with multimodal characteristics, including user-friendly interface, human–computer interaction and VR soundscape (therapeutic music, sound of waves, seagulls, footsteps, etc.) to strengthen immersion. Participants can interact in first-person perspective with the dynamic high-fidelity virtual environment by acting as a mouse pointer. Figure 3 shows the visual representations of the app content. Participants will be asked to install the app on their smartphones for free and instructed to use the app by the research nurse and provided with a user guide to introduce the functions in the app and provide solutions to problems, noting that the sessions should be completed in order and that each subsequent session will become available when the preceding one completed. Each participant will be assigned a unique key to login the app, while AC group will have no access to login to avoid contamination.

**Fig. 3 Fig3:**
[figure not shown]
The visual representations of the app content

The VR-CBT app is consisted of three parts, including health education, providing CBT techniques, e.g., relaxation techniques practices, which are more applicable to immersive environment with virtual soundscape for patients to ‘escape from’ their real world, and summary with quiz of current day’s session to examine whether patients master the techniques. The intervener is a digital human in the app, in this study, a virtual nurse whose speech and body language were well-designed by the research team. The dynamic high-fidelity virtual scenarios in the app include indoor environment and sunshine beach to increase interest and adherence. The virtual nurse will teach patients cognitive behavioral strategies and assign homework with virtual voice in indoor environment, where patients will interact with virtual nurse. On the contrary, patients will practice breath relaxation and muscle relaxation techniques in sunshine beach environment with therapeutic music and seaside soundscape. Patients will submit their weekly homework in ‘Homework’ section the main interface. Table 1 provides the schedule of the VR-CBT intervention. The contents were designed and reviewed by clinical nurse managers and psychotherapists from Sun Yat-sen University Cancer Center and School of Nursing, Sun Yat-sen University, Guangzhou, Guangdong province, China.

**Table 1 Tab1:** The schedule and details of the VR-CBT intervention

Stages	Sessions (Timepoint)	Themes	Contents	Assessments
Perioperative stage	1 (1 week pre-surgery)	What can I do with my anxiety and fear?	• Health education on diagnoses and treatments of CRC • Introduction to cognitive patterns of anxiety and fear as CRC patients • Breath relaxation technique with real-time assessment • Key points summary and quiz • Homework assignment: Patients record the use of breath relaxation technique	SSQ
	2 (1 week post-surgery)	Are my thoughts valid and useful?	• Health education on post-surgery early ambulation of CRC • Identification and evaluation of patients’ automatic thoughts towards CRC • Key points summary and quiz • Homework assignment: Patients record the automatic thoughts in the app	
	3 (2 weeks post-surgery)	Confrontation rather than avoidance	• Health education on enterostomy self-care or Kegel exercises • Effective behavioral strategies for adapting to the sick role • Appliance of behavioral experimental techniques to validate strategies • Key points summary and quiz • Homework assignment: Patients perform behavioral experiment and record results	
Rehabilitation stage	4 (3 weeks post-surgery)	My emotions are under my control	• Health education on physical activities of CRC survivors • Daily activities related to positive emotions • Muscle relaxation technique with real-time assessment • Key points summary and quiz • Homework assignment: Patients record the use of muscle relaxation technique	
	5 (4 weeks post-surgery)	Think it in a different way	• Health education on nutrition and dietary of CRC survivors • Psychoeducation of irrational illness and role beliefs • Key points summary and quiz • Homework assignment: Patients record the irrational and rational illness beliefs	
	6 (5 weeks post-surgery)	Actions speak louder than words	• Health education on health promotion behaviors of CRC survivors • Problem solving to the role maladaptation, including goal setting and time allocation • Key points summary and quiz • Homework assignment: Patients record behaviors that aim to adapt to the sick role	
	7 (6 weeks post-surgery)	Review and cope in the future	• Health education on follow-up visits of CRC survivors • Review the change of emotion, cognition, behaviors and CBT technique in the intervention • Gratitude to the participants and encouragement of coping in the future with CBT techniques	SSQ, semi-structured interviews

A master of Nursing Specialist who has undertaken the CBT training will monitor the adherence to the app protocol by tracking the number of sessions and homework that participants accessed in the backstage of app. Additionally, the intervention nurse will be responsible for checking the completion of patients submitted homework. More importantly, the intervention nurse will be tailored to address the issues patients encountered in completing homework.

The most common side effect associated with VR is simulator sickness, or VR sickness, cybersickness. It is a symptom similar to motion sickness that may manifest both during and after exposure to various VR environments, such as headaches, dizziness, and nausea during and after using VR devices [39, 40]. To reduce simulator sickness, we have paid extra attention to the various aspects of a VR system that contributed to users’ discomfort while designing the system. First, the app is based on desktop VR technique which is non-immersive and has the least potential for arising motion sickness. Second, the environment in VR-CBT app do not overly emphasize fast movement or rotation, and participants will have full control of their own motion in the VR environment. Third, to decrease the risk of dizziness, before entering the VR environment, the system will send prompt messages automatically to remind patients to avoid excessive movement or sudden head movements. Furthermore, we have increased and stabilized the frame rate (from 30 Frames Per Second to 60 Frames Per Second) to reduce the potential for dizziness, as the high display frame refresh rate is considered a crucial approach for alleviating the dizziness in VR applications [41]. In addition, the app improves the stability of VR scenario to reduce camera jitter or position changes that may cause dizziness.

Several strategies will be adopted to prevent attrition of study participants. Messages via WeChat will be sent weekly to keep in touch with patients after discharge. In addition, in the case of failure to reach participants, their main caregivers will be contacted. Incentives will be offered to all participants to expresses our gratitude when evaluating outcome variables at baseline, 1, 2 and 3-month post-intervention.

The intervention will be terminated if the participant declares he or she no longer wishes to participate, or is unable to continue the protocol treatment owing to adverse events. If the intervention proves to be effective, the VR-CBT app will be free available for participants enrolled in the AC group. Project management group meeting will be conducted weekly and blind information on the study.

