**Discussion:**

The positive outcomes and user experience of VR-CBT will advance researches on the effectiveness of psychosocial interventions that aims to promote adaptation to the unexpected sick role on cancer populations. This protocol can be tested as an accessible and feasible alternative to traditional high-cost treatment in a randomized controlled study to improve the outcomes of younger cancer survivors.

Trial registration.

The protocol was registered on 21 June, 2023 in Chinese Clinical Trial Registry (No.: ChiCTR2300072699) at https://www.chictr.org.cn/.

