A literature review showed that cognitive behavioral therapy (CBT) was one of the most common and effective intervention in improving QOL and alleviating adverse psychological effects among CRC survivors [20]. One explanation could be that CBT interventions for patients cover a wide variety of aspects, including social, psychological, and physical components, which can enhance QOL and alleviate negative psychological impacts [21]. However, the requirement for experienced practitioners and the time as well as the resources required to prepare one, hinders the widespread adoption of CBT in general practice [22]. With the growing proliferation of smartphones, CBT delivered by mobile application (app) becomes an attractive option since it is cost-effective and highly accessible. Interventions built upon CBT principles and delivered via a mobile app has been shown to be as effective as face-to-face CBT with stronger benefits in cancer patients [22, 23].

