**Fig. 1 Fig1:**
[figure not shown]
The causal model of this study

This study aims to develop a study protocol for a self-led VR-based CBT intervention to facilitate the sick role adaptation, modify irrational illness cognition, alleviate anxiety and depression, and improve QOL among working-age CRC patients and to evaluate its effectiveness.

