## Hypotheses

We hypothesize that that working-age CRC patients in the VR-CBT group, in comparison with participants assigned to the attention control (AC) group, will report significantly better adaptation to the sick role, more rational illness cognition, lower levels of anxiety and depression and better QOL, at 1, 2 and 3-month after the intervention.

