## Discussion

To the best of our understanding, this will be the first randomized controlled trial of a self-led VR-based CBT intervention for working-age CRC patients in China. If the intervention shows promising results and favorable user experience, it will generate new insights to the advancement of theoretical and practical knowledge of CBT interventions which focus on irrational illness belief, negative emotions and ineffective coping styles and aim to promote psychosocial adaptation. Furthermore, it will add to the evidence that self-led VR-based CBT has potential to serve as an accessible and feasible alternative to traditional high-cost treatment and applies in cancer survivorship care settings to improve the quality of patient-centered care and outcomes of younger cancer survivors.

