## Conclusions

This study will add to the existing body of knowledge and advance research in the field on the effectiveness of a self-led, VR-based CBT intervention targeted for psychosocial outcomes on cancer populations. If the VR-based CBT intervention demonstrates its effectiveness in improving sick role adaptation in working-age adults with CRC, the next step will be to popularize this type of intervention on negative emotions, illness perception and coping styles to address their psychosocial challenges and age-tailored concerns.

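### The VR-CBT arm receives the app plus tailored nurse help with homework, so a difference from attention control cannot be attributed to a self-led app

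*Protocol article*

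**What the plan says.** All references are to the protocol article.

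- **Aim (end of Background).** The study is to "develop a study protocol for a self-led VR-based CBT intervention to facilitate the sick role adaptation". The label self-led also appears in the abstract, the app description, the Discussion and the Conclusions.
- **Rationale (Background).** App delivery is motivated by the statement that "the requirement for experienced practitioners and the time as well as the resources required to prepare one, hinders the widespread adoption of CBT".
- **Deliverer (The VR-CBT intervention).** A digital human in the app is named as the intervener. This virtual nurse teaches the strategies and assigns the homework.
- **Human support (same section, after Table 1).** A nurse specialist with CBT training tracks sessions and homework through the app's back end. An intervention nurse checks homework completion, and the text adds, introduced as the more important point, that "the intervention nurse will be tailored to address the issues patients encountered in completing homework".
- **Comparator (The attention control intervention).** A clinical nurse contacts AC participants weekly through WeChat for 7 weeks, with standardised questions and general advice, on top of standard care.
- **Hypothesis.** VR-CBT participants, "in comparison with participants assigned to the attention control (AC) group, will report significantly better adaptation to the sick role".
- **Use of the result.** If the intervention is effective, AC participants are to be given the app free of charge. The Conclusions speak of the "effectiveness of a self-led, VR-based CBT intervention targeted for psychosocial outcomes on cancer populations" and of popularising this type of intervention as the next step. The abstract says that "This protocol can be tested as an accessible and feasible alternative to traditional high-cost treatment in a randomized controlled study", and the main Discussion that "self-led VR-based CBT has potential to serve as an accessible and feasible alternative to traditional high-cost treatment".

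**The concern.** The label and the delivery do not describe the same intervention. The argument for a self-led app is that skilled staff are scarce, yet the VR-CBT arm includes a person who gives individual help with homework. If the trial is positive, its report would credit a self-led app with an effect that may owe something to that person.

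A hospital that then offers the app without the nurse would be delivering something that neither arm tested. The Limitations section discusses unblinded participants and simulator sickness but not this point.

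**Working it through.** There is no stated figure to reproduce, and the point does not depend on sample size, power or significance level. The check compares what each arm receives.

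**Step 1. Contents of each arm.**

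| Component | VR-CBT | AC |
|---|---|---|
| Standard care | yes | yes |
| App with virtual nurse | yes | no (no login) |
| Weekly general nurse consultation | not described | yes, 7 weeks |
| Tailored nurse help with homework | yes, when problems arise | not described |

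Weekly WeChat messages to keep in touch after discharge are also planned, with no restriction to one arm.

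**Step 2. What the contrast estimates.** Relative to standard care, let A be the effect of the app, N the effect of tailored nurse help, I any interaction of the two, and C the effect of the AC consultations. Standard care cancels, so

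difference = (A + N + I) − C.

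The quantity that matches a self-led label is A − C. The two are equal only if N + I = 0. No arm receives the app without the nurse, so the design cannot test that condition.

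**Step 3. What the homework contains (Table 1).** Homework is set in sessions 1 to 6 and not in session 7.

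- Sessions 1 and 4: a log of relaxation practice.
- Session 2: a record of automatic thoughts.
- Session 3: a behavioural experiment.
- Session 5: irrational and rational illness beliefs.
- Session 6: behaviours aimed at adapting to the role.

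Some tasks are simple logs and others are close to the core of CBT. The text does not say whether the nurse's help is practical or therapeutic. App use has its own support, through instruction by the research nurse and a user guide.

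**Step 4. How much contact is possible.** The planned number is 30 per arm.

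- VR-CBT: at one contact per homework task, the ceiling is 6 × 30 = 180. Help depends on a problem arising, so the floor is 0.
- AC: 7 weekly contacts × 30 = 210 scheduled.

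By count, the AC arm may have as much human contact as the VR-CBT arm, or more. The imbalance is one of kind: tailored and tied to the CBT homework, against standardised and general.

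**Step 5. Whether the listed data could separate the parts.** Other measurements lists login counts and times, length of use, time per session, quiz results and interaction results. All come from the app's back end. Nurse contacts are not among the listed items.

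**Step 6. The wording about an alternative.** It occurs in the abstract's Discussion and the main Discussion, in hedged form. The only comparator is AC plus standard care, and no cost or resource-use outcome is listed. The trial can therefore speak to effectiveness against AC, but not to relative effect or cost against conventional treatment.

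**The case against.** The case on the other side has force in several places.

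- **The primary comparison is valid.** Randomisation gives an unconfounded effect of the package, and the stated hypothesis is superiority over AC. This stands. The point concerns what the effect is attributed to, not the test.
- **The nurse's role may be slight.** The specialist is described only as tracking use, and the intervention nurse checks completion, not content. A reader might infer that patients receive guided CBT from a person. The text does not say so, and practical troubleshooting is an equally possible reading. But the article sets no limit on the help and presents it as the more important part of the nurse's task, so it cannot be assumed to have no effect.
- **Attention is balanced.** It is in part, and the AC arm's scheduled weekly contact must be counted. Tailored homework support remains on one side only.
- **A contact log may exist elsewhere.** An article condenses the full protocol, so its silence is not a defect. The recommendation to log applies only if this is not already arranged.

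A stronger reading is also tempting: that the trial sets out to show a low-cost alternative to traditional CBT and fails for want of a CBT arm and cost data. The documents do not support this. The aim, the hypothesis and the Conclusions contain no such claim. The Discussion wording is conditional, refers to costly traditional treatment without naming CBT, and says accessible and feasible, not low-cost. A superiority hypothesis against AC needs neither a CBT arm nor a cost outcome.

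**Conclusion.** The article contradicts itself on what is being tested: a self-led app by name, an app with tailored nurse help by description. A difference between arms estimates the second. It cannot be credited to a self-led app, and it does not support offering the app alone.

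The size of the misattribution cannot be computed. It could be nil if the nurse is rarely needed or helps only with practical matters, and it could be material if she works on the content of the homework. The range of 0 to 180 contacts assumes 30 patients and at most one contact per homework task, and it says nothing about their effect.

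The conclusion rests on the article's description being complete as to which arm receives homework help. The planned comparison, the outcomes and the sample size are not affected. The change is worth making because it alters what the trial may conclude and because contact data are hard to recover afterwards.

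**What to change.** 1. In the aim, the app description and the conclusions, describe the tested intervention as nurse-supported: the app plus nurse homework support.
2. If the full protocol does not already provide for it, record prospectively the number, duration and topic of nurse contacts per patient in both arms. Report these descriptively only. Contacts occur after randomisation and are triggered by difficulty, so relating them to outcome would be confounded.
3. In the abstract's Discussion and the main Discussion, limit the wording about an alternative to costly treatment to effectiveness against attention control plus standard care.

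The cost is a few changes of wording, brief logging at each contact, and a more modest claim. Neither a conventional CBT arm nor a redesign of the app is needed. Moving homework feedback into the software would mean redevelopment and a changed intervention.

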## Outcome measures

### Primary outcome

The sick role adaptation will be measured using the Chinese version of Illness Behavior Questionnaire (IBQ). IBQ has been used to predict response to illness and treatment [42]. The Chinese version of IBQ could be divided into 3 dimensions, namely negative emotions, behavioral responses and the sick role [43]. The Chinese version of the IBQ has demonstrated acceptable internal consistency, with Cronbach’s α coefficient 0.680–0.765 [43].

### Secondary outcomes

The negative emotions will be assessed using the Hospital Anxiety and Depression Scale (HADS). It is a self-report questionnaire comprising subscales for anxiety and depression. A total of 14 items included in the scale, each of which is scored on a Likert 4-point scale from 0 to 3, with a total score of 0 to 7 for being asymptomatic, 8 to 10 for mild anxiety or depression symptoms, and 11 to 21 for significant anxiety or depression symptoms [44]. The Chinese version of HADS revealed a Cronbach's alpha coefficient of 0.88 [45].

The illness cognitions will be assessed using the Brief Illness Perception Questionnaire (BIPQ). The BIPQ consisted of nine items that examine the patient’s cognitive and emotional responses to illness [46]. The items address perceived consequences, timeline, personal control, treatment control, identity, concerns, comprehension, and emotional response. The final item is an open-ended response question that assesses causes of the illness. The Chinese version of BIPQ has been widely used as a screening tool for assessing illness perceptions in China, with the Cronbach's α and split-half reliability of BIPQ was 0.77 and 0.81 respectively [47].

The QOL will be assessed using the European Organization for Research and Treatment of Cancer Quality of Life Questionnaire-Core 30 (EORTC QLQ-C30) [48]. It includes five functional scales (physical, role, emotional, cognitive and social), three symptom scales (pain, fatigue and nausea/vomiting), one global health status scale and six single items of symptoms (e.g., insomnia). For both the overall scale and each scale, the raw scores are transformed into standard scores in the range of 0 to100. Higher scores on the scale indicate better QOL. The Chinese version of EORTC QLQ-C30 [49] has demonstrated satisfactory internal consistency reliability and structural validity.

### Other measurements

The socio-demographic and clinical characteristics of the participants will be collected, such as sex, age, educational level, marital status, household income per month, tumor location, stage and treatment modality.

Furthermore, semi-structured interviews will be employed to explore and gain insights into participants’ experiences and perceptions of the VR program until data saturation. The post-intervention interviews will be carried out following the completion of the final scheduled session and audio recorded after obtaining informed consent from the participants. Open-ended, probing questions will be used to guide the interview (Table 2). Content analysis approach will be applied to analyze the qualitative data.

**Table 2 Tab2:** Topic guide for post-intervention interview

1. When do you usually use the app? Why? 2. How do you feel about VR program? 3. What impressed you most in the VR program? 4. How the VR program help you adapt to the sick role and cope with CRC? 5. Have you experience any discomfort or difficulties during the usage of the VR program? Please tell me details. 6. What are your thoughts on the homework? 7. What advice would you give us on the VR program? 8. If there is a chance, would you recommend the VR program to other patients? Why?	

In addition, login counts and time, length of usage, time spent of each session, quiz results and results of human–computer interaction will be collected via backend monitoring data to evaluate the completion of the intervention. On the other hand, the privacy issues will also be seriously taken into account. First, the app will not collect the personal information that may recognize the patient identity such as name, age, residence and diagnosis. Second, the user data will be stored in password-controlled, restricted-access servers in the university to protect user information from loss, misuse, unauthorized access or disclosure, alteration, or destruction. Third, the user behavior data will only be used for statistical analysis and supervised by the Institutional Review Board of School of Nursing, Sun Yat-sen University.

